## Abstract

**Background:**

Cervical spondylosis is a very common disorder and cervical spondylotic radiculopathy (CSR) is the most common form of spinal degenerative disease. Its clinical manifestations focus on pain and numbness of the neck and arm as well as restricted movement of the neck, which greatly affect the patient’s life and work. The orthopedic of traditional Chinese medicine (TCM) theory holds that the basic pathologic change in spinal degenerative diseases is the imbalance between the dynamic system and the static system of the cervical spine. Based on this theory, some Chinese physicians have developed a balance chiropractic therapy (BCT) to treat CSR, which has been clinically examined for more than 50 years to effectively cure CSR. The purpose of this study is to evaluate the therapeutic effect and safety of BCT on CSR and to investigate the mechanism by which the efficacy is achieved.

**Methods/design:**

We propose a multicenter, parallel-group, randomized controlled trial to evaluate the efficacy and safety of BCT for CSR. Participants aged 18 to 65 years, who are in conformity with the diagnostic criteria of CSR and whose pain score on a Visual Analog Scale (VAS) is more than 4 points and less than 8 points, will be included and randomly allocated into two groups: a treatment group and a control group. Participants in the treatment group will be treated with BCT, while the control group will receive traction therapy (TT). The primary outcome is pain severity (measured with a VAS). Secondary outcomes will include cervical curvature (measured by the Borden Index), a composite of functional status (measured by the Neck Disability Index, NDI), patient health status (evaluated by the SF-36 health survey) and adverse events (AEs) as reported in the trial.

**Discussion:**

If BCT can relieve neck pain without adverse effects, it may be a novel strategy for the treatment of CSR. Furthermore, the mechanism of BCT for CSR will be partially elucidated.

**Trial registration:**

Clinical Trials.gov Identifier: NCT02705131. Registered on 9 March 2016.

## Background

Cervical spondylosis is a very common disorder and cervical spondylotic radiculopathy (CSR) is one of the most common patterns, accounting for about 60 to 70 % of all cervical spondylosis [1–3]. The incidence of CSR tends to increase year by year due to population aging, lifestyle changes and work or life stress. Its clinical manifestations focus on pain and numbness of the neck and arm as well as restricted movement of the neck, which greatly affect people’s lives and work. The agents currently approved for treatment and/or prevention of CSR include operative treatment and nonoperative treatment categories (including drugs, traction, manipulation, physical therapy, functional exercise, etc.), but many studies have confirmed that nonoperative therapy has more evident effects on the optimized scheme of CSR [4–6]. Among them, manipulation is the most common therapy for CSR due to its low risk, good therapeutic effect, ease of operation and its economics [7, 8]. However, as there are many kinds of manipulations with different efficacy standards, treatment and operation standardization and evaluation mechanisms, it is not conducive to the long-term development of massage, which could result in the problem of choice and multiple choices easy to cause medical information source waste. Moreover, there are currently few randomized, parallel-controlled trials to verify its efficacy in treating CSR.

From this we have developed a balance chiropractic therapy (BCT) to treat CSR, which has been clinically examined as effective at curing CSR for more than 50 years, and we examine the therapeutic effect and safety of BCT to improve the syndrome experienced by CSR patients in a multicenter, randomized, parallel-controlled trial. The results of this study will provide evidence regarding the value and safety of BCT as an intervention to improve the syndrome in CSR-affected individuals. Furthermore, we speculate the mechanisms of action can be partially identified by this study.

## Methods/design

### Study design

This clinical trial is a multicenter, parallel-group, randomized controlled design. Subjects will be enrolled at four hospitals: (1) The affiliated Hospital of Shaanxi University of TCM; (2) Shaanxi Provincial Hospital of TCM; (3) Xi’an Municipal Hospital of TCM; and (4) The Red Cross hospital of Xi’an.

### Ethical issues

This study has been approved by the Ethics Board of Shaanxi University of TCM (No: SZFYIEC-PJ-2016[01]). Each participating center obtained local Institutional Review Board approval. All study participants will sign the written informed consent prior to participation.

### Patients population and recruitment procedure

The study population consists of individuals aged 55 to75 years with CSR. The diagnostic criteria of CSR are referred to in the *Guidelines for the Diagnosis and Treatment of Cervical Spondylosis (2011 edition)* promulgated by the Chinese Association of Rehabilitation Medicine’s cervical spondylosis branch. The symptoms and signs include syndromes of pain and numbness distributing along spinal nerve roots and having positive intervertebral foramen extrusion and/or brachial plexus pull tests. Moreover, the clinical manifestations and imaging are consistent with the clinical syndromes.

Subjects will be excluded if they have disorders such as thoracic outlet syndrome, tennis elbow, carpal tunnel syndrome, cubital tunnel syndrome, periarthritis of the shoulder, tenonitis of biceps brachii, or a diagnosis of acute spinal cord injury, acute spinal cord inflammation, or symptoms of cervical vertigo and abnormal changes on transcranial Doppler (TCD). Subjects will also be excluded if they have associated pathologies of the liver, kidney, hematopoietic endocrine, cardiovascular or nervous systems and other severe primary diseases, or fractures, osteoarticular tuberculosis, osteomyelitis, bone tumor, severe osteoporosis, or mental disabilities, or other bodily weaknesses that cannot withstand the stimulation of BCT. Moreover, the trial will exclude individuals who have any acute infectious disease, gastric or duodenal ulcer with acute perforation, or treated areas of severe skin damage or skin diseases. In addition, subjects who have received surgical treatment for CSR or neck injury, or have received radiofrequency therapy to a cervical intervertebral disc, minimally invasive surgery, ozone, acupuncture and moxibustion, other manipulations or block therapy within 2 weeks, will also be excluded, as will lactating or pregnant female patients and patients who are participating in other clinical trials related to cervical spondylosis.

This study is to be conducted in accordance with patient protection principles as outlined in the Declaration of Helsinki, and approved by the appropriate Institutional Review Boards. Each participant will sign the written informed consent before undergoing any examination or study procedure in compliance with Good Clinical Practice. We will utilize a central randomization management system (CRMS) to identify all persons aged 18 to 65 years who meet the diagnostic criteria of CSR and who have a pain score on a Visual Analog Scale (VAS) of more than 4 points and less than 8 points. Patients who initially meet these eligibility criteria will then complete the additional baseline testing (mainly including a VAS, the Borden Index, the Neck Disability Index (NDI) and the 36-item Short Form health survey (SF-36) and will be randomized into either the treatment or the control group.

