### Randomization and allocation

This clinical trial is a multicenter, randomized, parallel-controlled design. Randomization and sectionalization of subjects will occur centrally using a CRMS and patients will be randomly generated codes according to the treatment group or the control group in a 1:1 ratio. Potential participants will be identified via databases of four hospitals and then interviewed by phone for interest and eligibility.

When the participants meet the inclusion or exclusion criteria and have signed the Informed Consent Form, researchers will access the CRMS and then input stratification factor according to the system’s prompt. The CRMS will display a participant identification code and a random number. The participant identification code or the random number is the only form of patient identity that distinguishes the treatment group from the control group. The flow of participants in the study, including the numbers analyzed for short-term and 6-month follow-up, are shown in Fig. 1.

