### Sample size considerations

We calculated the sample size for this two-arm trial on the basis of comparing BCT versus TT, using the superiority test formula:$$ {n}_1={n}_2=2{\left[\left(ta+t\beta \right)s/\delta \right]}^2, $$where *tα* and *tβ* are constants, *s* is the estimated standard difference and *δ* is the mean value of the VAS for neck pain. The patients’ numbers were arranged in equal proportion and a superiority one-sided test was employed. Setting alpha at 0.05 and beta at 0.1, the calculated sample size of each group is around 98. Considering 20 % loss to follow-up, the total sample size needed to detect this difference at a 5 % level of significance with a power of 90 % is 240 patients [15, 16].

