### Trial status

The trial is still recruiting at the time of submission. The first participant was enrolled on 2 August 2016. The trial is expected to complete in August 2017.

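### The eligible age range contradicts itself: 55 to 75 years where the study population is defined, 18 to 65 years in the abstract and in the identification step

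*Protocol article*

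**What the plan says.** The article states the age criterion three times.

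- **Patients population and recruitment procedure, opening sentence:** "The study population consists of individuals aged 55 to75 years with CSR".
- **Same section, later, on the CRMS:** the system will be used to "identify all persons aged 18 to 65 years who meet the diagnostic criteria of CSR", with a further condition on the pain score. The next sentence treats these items as eligibility conditions for going on to baseline tests and randomisation: "Patients who initially meet these eligibility criteria will then complete the additional baseline testing".
- **Abstract, Methods/design:** "Participants aged 18 to 65 years, who are in conformity with the diagnostic criteria of CSR".

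Three other statements bear on how the criterion is applied. Study design: "Subjects will be enrolled at four hospitals". Randomization and allocation: "Potential participants will be identified via databases of four hospitals and then interviewed by phone for interest and eligibility". Trial status: "The trial is still recruiting at the time of submission".

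**The concern.** Both limits differ, the lower (55 against 18) and the upper (75 against 65), so the conflict is more than one mistyped figure. Neither range is presented as a stratum, a subgroup or a target within the other. All the statements are current text.

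Age is a basic entry criterion, and several things hang on it:

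- whether a given candidate may be randomised;
- which randomised patients count as eligibility deviations;
- the population that the final report may claim to describe.

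The text also leaves room for the conflict to matter in practice. Hospital staff screen for eligibility by telephone and so must apply some age limit at that step, and recruitment was open when the article was submitted. A statistical analysis plan could not settle the matter, because it does not decide who is eligible.

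**Working it through.** The plan gives no computed figure on this point to reproduce. The check is a comparison of the stated ranges; it does not involve the sample size, the power or the significance level.

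**Inputs**

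- Range A, 18 to 65 years: abstract, and the CRMS identification step in the recruitment section.
- Range B, 55 to 75 years: opening sentence of the recruitment section.

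**Counting rule:** whole years of age, both limits included, so years = upper − lower + 1.

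| Set | Ages | Calculation | Years |
|---|---|---|---|
| Range A | 18–65 | 65 − 18 + 1 | 48 |
| Range B | 55–75 | 75 − 55 + 1 | 21 |
| In both | 55–65 | 65 − 55 + 1 | 11 |
| In either | 18–75 | 48 + 21 − 11 | 58 |
| Only in A | 18–54 | 48 − 11 | 37 |
| Only in B | 66–75 | 21 − 11 | 10 |

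**Shares**

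- Common to both, of all ages in either range: 11/58 = 19%.
- Of range A, also in B: 11/48 = 23%, which leaves 37/48 = 77% outside B.
- Of range B, also in A: 11/21 = 52%, which leaves 10/21 = 48% outside A.
- Ages whose eligibility depends on which statement is followed: (37 + 10)/58 = 47/58 = 81%.

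**Sensitivity to the counting rule.** If the ranges are measured as widths instead, they are 47 and 20 years, with an overlap of 10 and a span of 57. The shared part is then 10/57 = 18%, so the picture does not change.

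**What the figures do not show.** They count years of age, not patients. The article gives no age distribution for the source population or for those enrolled, so the share of patients in the disputed ages cannot be estimated. It could be small or large.

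**The case against.** The strongest reply is that this is a slip in a condensed article. Two of the three statements agree, one of them in the operational recruitment step, and only an introductory sentence differs. The sites presumably work from the full protocol, which is not shown and may be consistent. That stands as a limit on the consequences: the article cannot show that any site used the wrong range. It does not remove the contradiction. An article may leave detail to the full protocol, but this one states the criterion and states it in two incompatible ways.

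Three stronger readings are tempting, and the document does not support them.

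- **A reader might infer that the CRMS enforces 18 to 65, so that 55 to 75 must be the error.** The text says only that the system will be used to identify such persons. It describes no age lock. The section on randomisation has candidates found through hospital databases and interviewed by telephone, and researchers enter the CRMS after the criteria are met and consent is signed. Two statements against one is not proof of which range was approved. Nor is the exclusion of pregnant or lactating women, although it has little purpose in a population that starts at 55.
- **A reader might infer that the four hospitals are enrolling different populations.** That is possible, but not shown. If the CRMS did apply one range, it would block part of such a divergence.
- **A reader might infer that 77% or 81% of patients are affected.** Those are shares of years of age. Quoting only the 77% would also be one-sided, since about half of the 55 to 75 range lies inside the other.

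On safety, the ranges differ in whether patients aged 66 to 75 may receive the neck manipulation. That follows from the text, but age is not the only safeguard: the exclusions for severe osteoporosis, fractures, cardiovascular and nervous-system disease and general frailty apply at any age. They do not settle the age conflict.

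**Conclusion.** The age criterion is wrong as written. This is an internal contradiction in a core eligibility criterion, not a debatable design choice. The two ranges agree on 11 of 58 whole years of age, and for the other 47 a patient's eligibility depends on which sentence is read. Until this is resolved, the population to which the result applies is undefined, and eligibility deviations by age cannot be identified consistently.

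The conclusion rests only on the three statements and on an inclusive count of whole years. It assumes nothing about which range is right, how the CRMS is configured or what the sites have done. The number of patients affected is unknown. The statement that recruitment is open holds as of submission; the first participant was enrolled on 2 August 2016 and completion was expected in August 2017.

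**What to change.** 1. Confirm the age range in the ethics-approved protocol and correct the abstract, the opening of the recruitment section and the CRMS identification step to that one range. The choice belongs to the sponsor and the approved document; this review does not presume it.
2. Verify that the CRMS and the telephone screening at all four hospitals apply the confirmed range, and state whether the CRMS blocks randomisation outside it.
3. Check the age at entry of every patient already randomised. Keep any patient outside the confirmed range in the intention-to-treat analysis, in line with the principle stated under Statistical analysis, and report each as an eligibility deviation.
4. Describe the target population in the final report by the confirmed range, with the observed ages by group.

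The cost is a short textual correction, one check of the CRMS settings and site screening instructions, and one listing of ages already collected. Sample size, randomisation and outcome schedule need no change on account of this point.

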### Interventions

Eligible patients will be randomized to one of the two arms: the treatment group and the control group. In the treatment group, patients will receive BCT for 20 days, while patients in the control group will receive traction therapy (TT) for 20 days. This study will be administrated at four hospitals. Patients will visit the physician at 1- and 3-month follow-up.

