### Control group

In the control group, patients will received TT. The patient is sitting comfortably and wearing a cloth bag for occipital-jaw traction, with their head bending forwards at an angle of about 10–15°. The traction weight for cervical spondylosis starts at 3 kg and gradually increases to the maximum weight of 6 kg in increments of 0.5 kg each time. The treatment is performed 30 min at a time every other day for a total of 10 times in 20 days.

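### The 2-week prior-treatment exclusion covers manipulation but not traction, so the VAS comparison can tilt towards BCT, by an unknown amount, relative to patients not recently treated

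*Protocol article*

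**What the plan says.** All references are to the protocol article.

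- **Exclusions** (Patients population and recruitment procedure). An itemised list of recent treatments bars entry. It names disc radiofrequency, minimally invasive procedures and ozone, and ends "acupuncture and moxibustion, other manipulations or block therapy within 2 weeks, will also be excluded". Traction appears neither there nor in any other exclusion.
- **Comparator** (Interventions; Control group). "patients in the control group will receive traction therapy (TT) for 20 days". Traction is the whole control treatment.
- **Traction and manipulation are separate categories** (Background). The existing nonoperative options are given as "drugs, traction, manipulation, physical therapy, functional exercise".
- **Pain at entry** (Patients population and recruitment procedure). A patient needs a "pain score on a Visual Analog Scale (VAS) of more than 4 points and less than 8 points".
- **Source of patients** (Randomization and allocation). "Potential participants will be identified via databases of four hospitals", followed by a telephone interview. Staff then "input stratification factor according to the system’s prompt"; the factor is not named, and nothing printed links it to prior treatment.
- **Content of BCT** (Treatment group). The procedure includes manual upward pulling on the neck, and a further vertical pull during rotation.

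**The concern.** The look-back names the class of treatment to which the experimental arm belongs and leaves out the treatment given in the control arm. A site that follows the rule must reject a patient who had manipulation last week, and may accept one who had traction last week and is still inside the pain window.

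Randomisation balances the number of such patients between arms, but not what happens to them next. In the TT arm they repeat a treatment that has recently left them with qualifying pain; in the BCT arm they move to a different package. If they respond less well to repeated traction, the average TT response falls. The corresponding group on the other side, patients still in pain after recent manipulation, has been removed from both arms.

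This would not show in a baseline table, because the arms would be balanced on it. The covariate adjustment described under Statistical analysis is triggered by baseline differences between groups, and adjusting for a main effect would not remove an interaction between prior traction and treatment. At stake is how far the primary VAS result applies to patients who have not just had traction.

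**Working it through.** **1. Is the asymmetry in the text?** The exclusion list names manipulation and does not name traction. Background lists the two as separate treatments, so the manipulation item cannot be read to cover traction. The control arm is traction. The asymmetry is therefore a stated rule.

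**2. What the plan's own figures give.** Sample size considerations states about 98 per group, one-sided alpha 0.05, beta 0.1, 20 % loss and 240 in total.

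- Total: 98/0.8 = 122.5, so 123 per arm and 246 in all; or 98 × 1.2 = 117.6, so 118 per arm and 236 in all. The stated 240 lies between them. This point does not depend on it.
- The 98 cannot be rebuilt, because no values are printed for the difference or the SD. Solving n = 2[(zα + zβ)s/δ]² for δ/s gives √(2/98) × (1.645 + 1.282) = 0.1429 × 2.927 = 0.418. The implied detectable difference is 0.418 SD, or about 8.4 mm **if** the SD is 20 mm (assumed).

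**3. Form of the tilt.** Let *p* be the share of participants with traction in the 2 weeks before entry, the same in both arms by randomisation. Let d_TT and d_BCT be the amounts by which their improvement falls short, under each treatment, of that in patients not recently treated. Then

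observed BCT advantage = advantage in patients not recently treated + p × (d_TT − d_BCT).

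Only the difference between the two shortfalls matters. The tilt is zero if p = 0 or if the shortfalls are equal.

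**4. Illustrative size.** The document gives neither *p* nor the shortfalls. Assume p = 10–40 % and SD = 20 mm. The standard error is 20 × √(2/98) = 2.86 mm. The last column is P(Z > 1.645 − tilt/2.86): the chance that the one-sided 5 % test favours BCT when the two treatments are equal in patients not recently treated.

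| p | d_TT − d_BCT | Tilt | Share of 8.4 mm | Chance of favouring BCT |
|---|---|---|---|---|
| 0 % | any | 0 mm | 0 % | 5 % |
| 10 % | 5 mm | 0.5 mm | 6 % | 7 % |
| 20 % | 10 mm | 2 mm | 24 % | 17 % |
| 40 % | 10 mm | 4 mm | 48 % | 40 % |

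If BCT suffers half the shortfall that TT does (d_TT = 5–10 mm, d_BCT = 2.5–5 mm), each non-zero tilt is halved, and the range becomes 0.25–2 mm.

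**5. What the last column is not.** When the tilt is above zero, BCT really is better on average in the enrolled population, so a rejection there is correct. The column shows how often the trial would suggest an advantage that does not hold in patients without recent traction.

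**The case against.** The other side has several good points, and most of them limit the claim.

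- **BCT also pulls on the neck.** A reader might infer that only the TT response is lowered. The Treatment group section does not support that: part of BCT is manual pulling, so patients who gained little from traction may gain less from BCT too. This stands, and is why the working uses a difference of shortfalls.
- **Qualifying pain is not non-response.** A reader might take every such entrant for a traction failure. A patient who fell from 7.5 to 5 points has responded and still qualifies, and so might one who had a single session, against a trial course of 10. This stands and lowers the average shortfall.
- **The window is short.** Patients in whom manipulation failed more than 2 weeks ago can enter, and could pull the comparison the other way. Background calls manipulation the commonest therapy for the condition. So the overall direction, across all prior treatment, is not established. The 2-week rule itself still acts on one modality only.
- **The list has other gaps.** Drugs, physical therapy and functional exercise are not listed either, but none of them is a trial arm. The manipulation item might also mean manipulations other than BCT, which softens the contrast; manipulation as a class is still screened and traction is not.
- **Inflated type I error.** A reader might infer this from the 7–40 % figures. It does not follow: randomisation keeps the test valid in the population enrolled.
- **Exposure is not shown.** Recruitment from hospital databases does not establish that candidates had traction recently, and the share could be close to zero.
- **The article is a summary.** The stratification factor is unnamed and the full protocol may handle prior treatment. But the exclusion is printed as an itemised, time-limited rule, and it is that rule which is uneven.

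None of this explains why recent use of one trial modality is screened and recent use of the other is not.

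**Conclusion.** The point holds as a possible tilt of unknown size. It rests on two assumptions: that some participants had traction shortly before entry, and that these patients fall short by more under TT than under BCT. Both are plausible and neither is documented. Under the assumed inputs the tilt is 0.5–4 mm; the upper end needs 40 % of all participants to have had traction within 14 days and a net loss of 10 mm in each, so it is an extreme case. If either assumption fails, the tilt is nil.

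The consequence is a limit on interpretation: a BCT advantage could in part reflect the recent treatment history of those enrolled. The documents do not support saying that the trial is biased towards BCT overall or that its error rate is wrong. This is a cheap improvement, worth making because the article reports recruitment still open at submission.

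**What to change.** 1. **Eligibility.** Add traction to the existing 2-week list under Patients population and recruitment procedure, so that the protocol's own look-back treats both trial modalities alike. If the full protocol already does this, align the article with it.
2. **Patients already randomised.** Establish from pre-randomisation records, in the same way in both arms, who had traction in the 2 weeks before entry. Pre-specify a sensitivity analysis of the primary VAS comparison without them. Because this is a pre-randomisation characteristic, leaving them out keeps a randomised comparison.

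**Cost.** A short amendment; some candidates wait up to 2 weeks or are lost; one extra analysis. That analysis is less precise: dropping 10–40 % of each arm multiplies the standard error by 1/√0.9 = 1.05 to 1/√0.6 = 1.29. It should therefore be read for the shift in the estimate and its interval, not for whether it crosses the significance limit.
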